### Measures

Measures will be collected at baseline, 6 months (end of intervention), and 12 months unless otherwise noted. Assessments will not be blinded. All measures will be completed by participants online via the app or LimeSurvey or are objective measures (eg, device downloads, HbA_1c_ tests, or recorded directly via the app).

#### Demographic Characteristics

At baseline, demographics will be collected (eg, age, sex, race/ethnicity, insurance type). We will assess socioeconomic status using a single item measure appropriate for young adults [69]. We will assess diabetes indicators (eg, duration of diabetes, device use, past 12-month frequency of severe hypoglycemic events defined as episodes of documented or presumed low blood glucose that resulted in seizure or loss of consciousness [70] and hospitalization for diabetic ketoacidosis). Additionally, we will ask if the participant has been suspected of having a COVID-19 infection.

#### Primary Outcome

The primary outcome will be HbA_1c_ assessed using a Clinical Laboratory Improvement Amendments–waived nonfasting whole blood HbA_1c_ test (AccuBase A_1c_ test kit by DTI Laboratories) mailed to the participant (with a postpaid return envelope) at each assessment. Samples are stable at room temperature for 21 days after collection, and results are available within 48 hours of receipt. AccuBase is FDA-cleared and uses capillary tube collection. Lab testing uses high-performance liquid chromatography, including abnormal hemoglobin screening. This method has been used effectively in a large national web-based study [71].

#### Secondary Outcomes

Secondary outcomes will include key self-regulation constructs including adherence, self-efficacy, and problem solving. Adherence to glucose monitoring and mealtime behaviors will be assessed during the 30 days prior to each assessment by calculating the percentage of days meeting each goal from device data. Diabetes management self-efficacy and outcome expectations will be assessed using the 10-item Self-Efficacy for Diabetes Management scale [72] that has shown strong relations with adherence among young adults with T1D [16]. Problem-solving skills will be assessed using the 10-item version of the Social Problem-Solving Inventory–Revised (α=.85) [73,74]. To assess symptoms of diabetes distress (a moderator), the 28-item T1-Diabetes Distress scale (α=.91) [75,76] will be used. Additionally, behavioral and emotional problems will be assessed with the 34-item version of the Counseling Center Assessment of Psychology Symptoms (α=.91 with all items), with the suicidality and desire to harm others items removed [77]. Self-regulation will be assessed using a brief self-regulation scale [78], a 12-item measure. Body awareness will be measured with the Body Awareness Questionnaire (18 items; α=.82) [79]. Hypoglycemia awareness will be measured by a single item [80]. Baseline levels of technology experience will be measured using the Technology Readiness Index (16 items) [81] and a novel measure based on Venkatesh et al [82] which asks about experience with specific types of technologies. We will also assess past 30-day substance use frequency (tobacco, alcohol, cannabis, other drugs) with items adapted from the 2018 Monitoring the Future survey [83], the National Survey on Drug Use and Health [84], and the Tobacco, Alcohol, Prescription medication, and other Substance use tool [85].

#### Implementation, Satisfaction, and App Metrics

For participants who receive human coaching, satisfaction with the human health coach will be assessed at the beginning, during, and the end of the program with the Session Alliance Inventory (α=.94) [86] and an adaption of the Working Alliance Inventory [87,88]. Satisfaction with the SweetGoals digital coach will be assessed at the beginning, during, and at the end of the program with the Session Alliance Inventory [86] and (at the end of the 6-month intervention period only) an adaption of the Working Alliance Inventory [87,88]. We will assess usability of the app components with items from the Usefulness, Satisfaction, and Ease of Use questionnaire (α=.98) [89] and overall app satisfaction with items adapted from Wixom & Todd [90] 3 times (early, midway, and at the end of the 6-month intervention period). In addition, the app will collect engagement metrics including the percentage of messages from digital coaches responded to within 24 hours of receipt and the mean length of the delay between when messages are sent by the app and accessed by the participant. These data will be used to explore objective app engagement and whether satisfaction and app engagement were better when receiving incentives or coaching.

#### Health Coaching Fidelity

Coaches will complete a detailed checklist after each meeting. In addition, fidelity coding of one randomly selected session for each participant will be completed [91]. Undergraduate coders will complete an extensive training protocol in the rating system. Coders will double code a randomly selected subset (25%) of sessions, and reliability will be tracked on an ongoing basis to ensure reliability of more than 80%.

### Statistical Analysis

All subjects, once randomized, will be included in the intent-to-treat sample. We will strive to collect all primary and secondary outcomes even if a participant does not engage in assigned interventions. Data will be stored in the Research Electronic Data Capture, MobileCoach, and a secure Dartmouth server.

#### Missing Data

As in any study, missing values may occur due to dropout (anticipated to be less than 20% by the end of 12 months), inability to reach a participant for follow-up, item nonresponse, or gaps in or missing device data. The proposed structural equation modeling (SEM) and linear mixed effects models (LMMs) use all available data and are robust to outcome data that are missing at random.

#### Primary Outcome Analyses

The primary aim is to test the main effects of incentives and coaching on HbA_1c_. We will also test the interaction between components (eg, the synergistic effect of adding one component to another). Two effect-coded indicators (see Collins [51] for detailed justification for using effect coding in the analysis of data from factorial designs) will be created, one for each component: the indicator for incentives (yes vs no) will differentiate between those offered incentives (coded +1; conditions 3 and 4 in Table 1) and those who were not (coded –1; conditions 1 and 2 in Table 1); the indicator for coaching (yes vs no) will differentiate between those offered coaching (coded +1; conditions 2 and 4 in Table 1) and those who were not (coded –1; conditions 1 and 3 in Table 1). To assess the impact of each component on HbA_1c_ over time (baseline, 6 months after, and 12 months after), an LMM will be fit. The model will include fixed effects for time, two component indicators, the component × component interaction, two component × time interactions, and the component × component × time interaction as fixed effects. The LMM will also include random effects for the intercept and time to account for within-person correlation. Based on this LMM, we will test the hypothesis that the yes level of each component (vs no) results in lower HbA_1c_ over time via the component × time interaction parameters.

We calculated the power for testing effects on HbA_1c_ based on the following assumptions: (1) models will include baseline HbA_1c_; (2) a within-person correlation between baseline HbA_1c_ and HbA_1c_ at each follow-up assessment of 0.6 (based on our pilot study); and (3) a standard deviation for HbA_1c_ of 1.2, based on our pilot data. Table 3 shows detectable main effects and interactions in terms of Cohen *d* [92] and HbA_1c_ mean differences. Given n=240 to n=270 (based on 80% to 90% retention), we will be able to detect small effect sizes (Cohen *d*=0.27 to *d*=0.29) with 80% power.

**Table 3 table3:** Aim 1 power for main effects and interaction between components.

Retention %	N	Power %	2-sided *P* value	Cohen *d*	HbA_1c_ difference %
90	270	80	.05	0.27	0.32
85	255	80	.05	0.28	0.33
80	240	80	.05	0.29	0.35

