Each component will take on 2 levels: yes or no. Note that the factorial design in Table 1 is not a 4-arm trial with each condition compared with a control or to each other. Instead, our interest is in tests of standard analysis of variance main effects and interactions [49]. These involve comparison of outcome means across multiple experimental conditions. For example, the main effect of the incentives component will be tested by comparing the mean of the outcome variable across the 2 conditions in which incentives will be delivered (ie, those in conditions 3 and 4; n=150 before attrition) versus the 2 conditions in which incentives will not be delivered (ie, those in conditions 1 and 2; n=150 before attrition). Hence, this main effect will be tested by comparing half of the sample (those offered incentives) versus the other half (those not offered incentives) in terms of the primary outcome. In this factorial experiment, each effect (including the interaction between the 2 components) will be estimated based on data from all 4 conditions (ie, the full sample) [48,50,51].

Figure 3 shows the study design. An online minimization program (MinimPy) will be used to assign participants [52]. Minimization assures similarity across intervention groups on multiple key covariates [52]. Differences between conditions will be minimized on gender, age, ethnicity (minority vs White), CSII versus MDI, CGM use, and HbA_1c_. Follow-ups will occur at 6 months and 12 months. Compensation will be $25 for the baseline assessment, $50 for each follow-up assessment, and a supplement of $50 for completing both follow-ups. This study was approved by the Committee for the Protection of Human Subjects at Dartmouth College and is registered at ClinicalTrials.gov [NCT04646473].

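### Table 3's 80% power is for a baseline-adjusted comparison, but the primary mixed model tests change from a freely estimated baseline, with about 70–76% power for a single contrast

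*Protocol article*

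**What the plan says.** All of this is in the protocol article, mainly under Statistical Analysis, Primary Outcome Analyses.

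- **Power basis.** "We calculated the power for testing effects on HbA_1c_ based on the following assumptions: (1) models will include baseline HbA_1c"; "a within-person correlation between baseline HbA_1c_ and HbA_1c_ at each follow-up assessment of 0.6 (based on our pilot study"; and "a standard deviation for HbA_1c_ of 1.2, based on our pilot data". "Given n=240 to n=270 (based on 80% to 90% retention"), the conclusion is that "we will be able to detect small effect sizes (Cohen *d*=0.27 to *d*=0.29) with 80% power". Table 3 gives d = 0.27, 0.28 and 0.29, and HbA1c differences of 0.32, 0.33 and 0.35, at N = 270, 255 and 240.
- **Primary model.** An LMM is fitted to HbA1c at baseline, 6 and 12 months. Its fixed effects are time, each component, their product, and the interaction of each of these three with time. Intercept and time are random. The hypothesis is that the active level of each component "results in lower HbA_1c_ over time via the component × time interaction parameters". No baseline covariate and no common-baseline constraint is listed, and time is not said to be linear or categorical.
- **Comparison.** Under Procedure, for incentives: "this main effect will be tested by comparing half of the sample (those offered incentives) versus the other half (those not offered incentives").

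**The concern.** The power calculation and the primary test sit in the same section but describe two different estimators. Conditioning on baseline leaves a follow-up variance of σ²(1 − r²). Subtracting a freely estimated baseline leaves 2σ²(1 − r), which is larger whenever r is below 1. The listed component terms give each component level its own baseline mean, so component × time measures a difference in change.

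If so, both primary hypotheses would be tested with less power than stated, in a trial that Procedure calls fully powered. The precision goes on estimating baseline differences that randomization already makes zero in expectation.

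**Working it through.** **Inputs** (Primary Outcome Analyses, Table 3, Procedure): two-sided 0.05; 80% power; r = 0.6; SD 1.2; N = 270, 255, 240; half the sample at each level of a component. The normal multiplier is 1.960 + 0.842 = 2.802.

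**Formulas.** With variance factor f and N/2 per level:

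- detectable d = 2.802 × √f × 2/√N
- power at a given d = Φ(d√N / (2√f) − 1.96)

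**Step 1: reproduce Table 3.**

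| Analysis | f | N = 270 | N = 255 | N = 240 |
|---|---|---|---|---|
| Unadjusted follow-up | 1 | 0.341 | 0.351 | 0.362 |
| Baseline-adjusted, 1 − r² | 0.64 | 0.273 | 0.281 | 0.289 |
| Change from baseline, 2(1 − r) | 0.80 | 0.305 | 0.314 | 0.323 |
| Table 3 | | 0.27 | 0.28 | 0.29 |

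Only the baseline-adjusted row matches. Multiplying its d by 1.2 gives 0.327, 0.337 and 0.347, within 0.01 of Table 3's HbA1c column.

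**Step 2: what the listed LMM tests.** With linear time, random intercept and slope, and complete data at 0, 6 and 12 months, the component × time estimate equals the between-level difference in 12-month minus baseline HbA1c. With categorical time, each interaction is change from baseline at that visit. Either way f = 2(1 − 0.6) = 0.80.

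**Step 3: power at Table 3's effects, complete data.**

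- N = 270, d = 0.27: 0.27 × 16.43 / 1.789 = 2.480; Φ(0.520) = 69.9%
- N = 255, d = 0.28: 0.28 × 15.97 / 1.789 = 2.500; Φ(0.540) = 70.5%
- N = 240, d = 0.29: 0.29 × 15.49 / 1.789 = 2.512; Φ(0.552) = 70.9%

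Detectable differences at 80% power are 1.2 × 0.305, 0.314 and 0.323, or 0.37, 0.38 and 0.39.

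**Step 4: sample size.** The penalty is 0.80/0.64 = 1.25, so 270 becomes 270 × 1.25 = 337.5, or 338. At exactly d = 0.27 the baseline-adjusted test needs 276 and the change test 345, again a ratio of 1.25.

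**Step 5: dropouts kept in the model** (generalized least squares, 300 at baseline, N at 12 months, effect sustained at both visits, 6-to-12-month correlation assumed 0.6):

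| Dropouts contribute | 12-month contrast | Linear slope |
|---|---|---|
| Baseline only | 71–73% | 71–74% |
| Baseline, and half also 6 months | 71–73% | 72–76% |

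If all dropouts have 6-month values, the 12-month contrast at N = 240 has 73–76% over assumed correlations of 0.5 to 0.8.

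**Step 6: joint 2-df test of both visits, categorical time, sustained effect.** This needs the 6-to-12-month correlation, which the article does not state. With complete data, power runs from about 78% (correlation 0.5, N = 240) to 66% (0.8, N = 270). At N = 240 and correlation 0.6, it is 76% if dropouts give baseline only and about 81% if they also give 6-month values. Over correlations 0.5–0.8 and these dropout patterns, the range is roughly 66–85%.

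**Step 7: check of the remedy.** The same calculation with component means constrained equal at baseline gives 79–80% for the 12-month contrast with complete data, which is Table 3's claim.

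**Sensitivity to r.** The ratio of the two factors is (1 − r²)/(2(1 − r)) = (1 + r)/2. At an effect giving 80% under adjustment, the change test has 68% at r = 0.5, 71% at 0.6 and 76% at 0.8.

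**The case against.** **The power assumption says the models include baseline HbA1c.** Adjustment may well have been intended, and a condensed article can leave a gap between two sentences. But the article states the fixed effects, the tested parameters and the power, and these conflict. In the listed model baseline enters as an outcome, which does not give the variance behind Table 3.

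**A flat 70% is not fixed by the document.** A reader might infer that the trial simply has 70% power. The text does not support that. It leaves the coding of time open, it speaks of parameters in the plural, and Missing Data says the models use all available data. Steps 5 and 6 show what follows: higher figures for a single contrast once dropouts contribute, and a joint test that can exceed 80% under favourable assumptions. A contrast averaging both follow-ups would have 76–86%, but the plan does not name it. This objection stands, and the size is given as a range.

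**Minimization includes baseline HbA1c.** Perfect balance would raise power only to 72–73%.

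**The sample size gap can be overdrawn.** A reader might set 345 against Table 3's 270. That would count the rounding of 0.273 to 0.27 as part of the model's penalty; the fair pairs are 276 to 345, or 270 to 338.

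**The LMM is a valid test.** This also stands. It is unbiased for the randomized effects and its type I error is unaffected. Only precision and the power statement are at issue.

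**Conclusion.** The point holds as a mismatch between the stated power and the specified model. Table 3 describes a baseline-adjusted comparison; the LMM as listed tests change from a free baseline. For a slope or single-visit contrast, power at Table 3's effects is about 70–71% with complete data and about 71–76% when dropouts contribute baseline or 6-month values. The detectable difference rises by about 0.04–0.05 HbA1c points, equivalent to a 1.25-fold sample size.

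These figures rest on the article's SD of 1.2 and r = 0.6, equal SDs at all visits, and a normal approximation. The dropout and joint-test ranges also rest on assumed 6-to-12-month correlations and dropout patterns. The documents do not support the inference that every reading of the model falls short of 80%, or that the primary analysis is invalid.

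**What to change.** Make the model and Table 3 describe the same test, in one of three ways:

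1. Analyse 6- and 12-month HbA1c as outcomes with baseline HbA1c as a covariate. Baseline must leave the outcome vector: adding it as a covariate while keeping it as an outcome leaves the component × time estimate unchanged.
2. Keep baseline as an outcome, but constrain the component means to be equal there by dropping the component and component × component terms at baseline.
3. Keep the LMM as written and restate Table 3 for it, with the time coding and the 6-to-12-month correlation given. For a single contrast with complete data the differences become 0.37, 0.38 and 0.39.

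Under the first two, also name the follow-up contrast that is tested; about 80% power is then restored at Table 3's effects.

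The cost is one paragraph of analysis wording or a revised table. No new data are needed, since HbA1c is already measured before randomization and at each assessment. The choice should be recorded before outcomes are compared between conditions.

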#### Secondary Outcome Analyses

Secondary analyses will evaluate change in 4 potential mechanisms of action of incentives and coaching (and their interaction) on HbA_1c_ at 6 months: glucose monitoring adherence, mealtime adherence, self-efficacy, and problem solving. We will follow the methods recently outlined for conducting mediation analysis in a factorial design with multiple mediators [93]. The mediation model will be tested using SEM with full maximum likelihood estimation, as outlined by MacKinnon et al [94]. The models will test effects of (1) each component and their interaction on the 4 mediators assessed at 6 months, (2) each mediator on HbA_1c_ at 12 months, and (3) each component and their interaction on HbA_1c_ at 12 months. Models will control for baseline levels of HbA_1c_ and the mediators. This model will evaluate the indirect effect of each component on HbA_1c_ through each mechanism, thereby testing whether the effect of coaching and incentives on HbA_1c_ is through increasing each of the 4 potential mechanisms.

#### Exploratory Analyses

Informed by the approach of Yardley et al [95], these analyses aim to determine whether app engagement and use metrics predict improvements on HbA_1c_ outcomes. We will first examine how engagement metrics differ between those receiving incentives versus no incentives and coaching versus no coaching. Use metrics will include the percentage of messages responded to within 24 hours of receipt and the mean length of the delay between when messages are sent and accessed. In LMM models predicting HbA_1c_, we will adjust for one or both components if we find significant component effects on engagement metrics. Effects of engagement metrics on HbA_1c_ outcomes are of interest in terms of future refinement and development of the SweetGoals app, suggesting critical app features that may be important to retain in future interventions or features that appear to have less impact and may need to be improved upon in future research [95].

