### Procedure

A fully powered 2×2 randomized factorial experiment (see Table 1) will be used to evaluate specific intervention components in terms of HbA_1c_ outcomes. Factorial designs are a highly efficient experimental approach for answering questions about the utility of multiple intervention components and their combinations. Data from these designs can be used to test the main effect of each intervention component as well as their interaction [47,48]. All participants will receive the SweetGoals app. Those assigned to the incentive group will receive incentives for meeting glucose monitoring and mealtime targets. Those assigned to the coaching group will receive web coaching in problem-solving skills focused on achieving better self-management and glycemic control. If assigned to incentives, participants will receive incentives weekly for 3 months, with gradually fading frequency over the next 3 months. If assigned to coaching, participants will meet with the coach weekly via web video for 3 months, with the frequency of those meetings also fading gradually over the next 3 months. The intervention period lasts for 6 months. Follow-up assessments will be completed at 6 months and 12 months after baseline.

**Table 1 table1:** Experimental conditions of the 2×2 factorial design.

Experimental condition	SweetGoals app	Incentives	Web coaching
1	Yes	No	No
2	Yes	No	Yes
3	Yes	Yes	No
4	Yes	Yes	Yes

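### The exploratory engagement models for HbA1c name no baseline participant characteristic as a covariate, so prior adherence or self-regulation can be mistaken for an app effect

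*Protocol article*

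**What the plan says.** The Exploratory Analyses section sets out linear mixed models predicting HbA1c from app engagement. On the aim: "these analyses aim to determine whether app engagement and use metrics predict improvements on HbA_1c_ outcomes". On the predictors: "Use metrics will include the percentage of messages responded to within 24 hours of receipt and the mean length of the delay" between a message being sent and being opened. On covariates it gives one rule: "we will adjust for one or both components if we find significant component effects on engagement metrics". No participant characteristic measured before the intervention is named.

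On interpretation: "Effects of engagement metrics on HbA_1c_ outcomes are of interest in terms of future refinement and development of the SweetGoals app", with the results "suggesting critical app features that may be important to retain in future interventions or features that appear to have less impact".

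Three other places bear on this:

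- Procedure: "All participants will receive the SweetGoals app". The app therefore has no randomized contrast.
- Secondary Outcomes: adherence is the percentage of days meeting each goal over the 30 days before each assessment, baseline included. "Self-regulation will be assessed using a brief self-regulation scale", and technology readiness is taken at baseline.
- Secondary Outcome Analyses: the mediation models do control for baseline HbA1c and the baseline mediators, which include both adherence measures.

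**The concern.** How quickly someone answers app messages is their own choice. The protocol's conceptual model (Intervention Model) holds that self-regulation drives adherence and HbA1c. The same trait could plausibly drive prompt responding. If it differs between participants before they open the app, engagement and later HbA1c will be associated even when the app does nothing. Adjusting for incentives and coaching does not remove this, because the difference exists within each randomized group.

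What is at stake is the use the plan makes of the result. An association caused by who the participants already were could be read as evidence that a feature works and should be retained, or that another has little impact. The randomized tests of incentives and coaching do not depend on these models.

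**Working it through.** **Plan's own figure.** The engagement models have no stated figure. Table 3 (primary aim) supplies the inputs, so I reproduced it first. With baseline adjustment, d = (z₀.₉₇₅ + z₀.₈₀) × √(4/N) × √(1 − 0.6²). For N=240 this is 2.802 × 0.1291 × 0.8 = 0.289. For N=255 and N=270 it is 0.281 and 0.273. The table gives 0.29, 0.28 and 0.27, so the inputs are consistent.

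**Inputs from the protocol (Primary Outcome Analyses).** N = 240 to 270; baseline to follow-up correlation 0.6; SD of HbA1c 1.2.

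**Assumed inputs (not in the document).** A baseline trait A, such as prior adherence. Its correlation with engagement is a = 0.2 to 0.5. Its standardized effect on follow-up HbA1c given baseline HbA1c is b = 0.1 to 0.3, in the direction of lower HbA1c. Its correlation with baseline HbA1c is −ρ, with ρ = 0.3 (also tried at 0.2). The true effect of engagement is zero.

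**Model, in SD units.** Follow-up = c × baseline − b × A + error, with c = 0.6 − ρb so that the correlation stays at 0.6.

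**Expected spurious slope per SD of engagement**

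- Baseline HbA1c as a covariate: −ab(1 − ρ²)/(1 − a²ρ²). For a=0.3, b=0.2, ρ=0.3: −0.06 × 0.91/0.9919 = −0.055 SD; × 1.2 = −0.066 HbA1c points.
- Change from baseline: a[(1 − c)ρ − b]. For the same values c = 0.54, giving 0.3 × (0.46 × 0.3 − 0.2) = −0.0186 SD; × 1.2 = −0.022 points. The slope is smaller because participants with more of the trait start lower and tend to fall less, which offsets part of the bias. At b=0.1 the bracket is 0.43 × 0.3 − 0.1 = +0.029, so the sign even reverses.

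**Simulated false-positive rates** (4,000 runs per row, N=240, ρ=0.3, two-sided 5%; single-follow-up regressions as a stand-in for the mixed model):

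| a | b | Baseline HbA1c as covariate | Change contrast | Baseline HbA1c and trait as covariates | Spurious slope, covariate model (HbA1c points per SD) |
|---|---|---|---|---|---|
| 0.2 | 0.1 | 6.3% | 5.4% | 5.0% | −0.022 |
| 0.3 | 0.2 | 18.8% | 6.0% | 4.9% | −0.066 |
| 0.5 | 0.2 | 42.9% | 8.4% | 5.6% | −0.112 |
| 0.5 | 0.3 | 76.9% | 26.7% | 5.2% | −0.168 |

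At N=270 with ρ=0.3 the maxima are 81% (covariate) and 29% (change). At N=240 with ρ=0.2, the weakest setting (a=0.2, b=0.1) gives 6.6% and 5.4%, and the strongest (a=0.5, b=0.3) gives 79.9% and 43.0%. Across repeat runs at N=240 the ranges are about 6% to 82% for the covariate model and about 4% to 45% for the change contrast. If the autoregressive slope rather than the correlation is held at 0.6, with ρ=0.2, the maxima rise to about 85% and 55%. Adding the trait brings the rate to about 5% in every setting, but the simulation measures the trait without error.

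**Which model applies.** The only mixed model specified in detail (Primary Outcome Analyses) keeps baseline HbA1c as an outcome and tests component by time. The engagement section speaks of predicting improvement. The change contrast is therefore probably the closer stand-in.

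**The case against.** The strongest reply is that this is one paragraph of a journal article. Covariate lists and metric definitions usually sit in an analysis plan, and the section leans on a cited approach that is not at hand. It is headed exploratory, it speaks of prediction, and its conclusions are hedged. Every input that drives the bias is assumed, and under a change contrast the weak settings stay at the nominal rate.

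Much of that stands. The fair statement is that the article names no baseline adjustment. A reader might infer that the models will never adjust for baseline characteristics, but a fuller covariate list may exist elsewhere. The low severity and the uncertain size also stand.

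The appeal to condensation does not fully answer the point. The section states an adjustment rule, and that rule covers only the components. The mediation section just before it, equally condensed, names its baseline covariates. The exploratory label also does not undo wording that calls the coefficients effects and uses them to choose features.

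A reader might also infer that engagement is measured over the same months as HbA1c, so that a worsening course produces low engagement. The documents do not support this. Neither Exploratory Analyses nor Implementation, Satisfaction, and App Metrics states a measurement window. Overlap is plausible for the 6-month HbA1c. The 12-month value comes six months after the intervention ends. Nor is there a basis for requiring that engagement be cut off at 12 weeks, which would discard the fading period in weeks 12 to 25.

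**Conclusion.** The point holds in a limited form. As written, the engagement models adjust at most for the randomized components, while a self-selected exposure is read as an effect of app features. Pre-existing adherence or self-regulation can therefore pass for an app effect.

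The size cannot be fixed from the document. Under the assumed ranges the false-positive rate is about 6% to 82% with baseline HbA1c as a covariate and about 4% to 45% for a change contrast. It is near nominal if the trait is only weakly related to engagement or to HbA1c. The upper figures should not be quoted as the expected error: they need the strongest assumed links, and 82% also needs the covariate form of the model. Severity is low, because the analysis is exploratory and no randomized comparison depends on it.

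**What to change.** In every exploratory model relating engagement to HbA1c, include these baseline covariates: the percentage of days meeting each adherence goal, the brief self-regulation score, technology readiness, and HbA1c. If baseline HbA1c is kept as an outcome, enter the other three with their time interactions instead. Report the result as an association that may retain residual confounding, and replace the wording about effects of engagement and features to retain accordingly.

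The cost is a few degrees of freedom in an exploratory model and a change of wording. The protocol already collects all four measures. The covariates are imperfect measures of the underlying traits, so they will reduce the bias rather than remove it.
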